Body temperature	Record body temperature every 8 h		×
WBS	Record WBS score every 24 h		
TCM sore throat symptoms	Record TCM sore throat symptoms every 24 h		
TCM symptom grading scale	×	×	
Blood/urine routine tests^a^	×	×	
C-reactive protein^a^	×		
Electrocardiogram^a^	×	×	
Liver/kidney function tests^a^	×	×	
Logcard distribution/collection	×	×	
Drug dispensing/collection	×	×	
Concomitant medication records	×	×	×
Adverse event monitoring		×	×

^a^
Notes: Means laboratory test items. Baseline tests may be waived if recent (<48 h) results are available. Post-treatment tests require participant/guardian consent. Liver/kidney function tests are optional based on clinical necessity.

### Safety assessments

#### Safety evaluation metrics

Safety assessments encompass three components: (1) clinical adverse reactions, monitored continuously post-treatment; (2) vital signs (blood pressure, respiratory rate, body temperature, and heart rate), measured at baseline and treatment endpoint; (3) laboratory tests, including complete blood count (WBC, RBC, HGB, PLT, NEUT, NEUT%, LYM%), C-reactive protein, urinalysis (WBC, RBC, GLU, PRO), liver function (ALT, AST, ALP, GGT/γ-GT, TBIL), renal function (BUN, Cr), and electrocardiogram. Pre-existing laboratory results within 48 h prior to enrollment may exempt retesting. Post-treatment laboratory tests (after 5 ± 1 day of medication) will be performed with participant/guardian consent. Liver and kidney function tests are optional based on clinical necessity. The incidence of adverse reactions serves as the primary safety endpoint.

#### Adverse event (AE) management

Definition: AEs refer to any unfavorable medical occurrences post-treatment, regardless of causality. Severity is classified using the NCI-CTCAE v5.0 criteria: Grade 1 (mild), Grade 2 (moderate), Grade 3 (severe), Grade 4 (life-threatening), and Grade 5 (fatal) (U.S. Department of Health and Human Services, 2025). Management includes: (1) continuing treatment with observation for mild AEs; (2) discontinuing treatment without intervention for moderate AEs; or (3) halting treatment and administering rescue therapy for severe AEs. For serious AEs (SAEs), immediate trial termination, emergency unblinding (if required), and prompt reporting to sponsors and ethics committees are mandated. All AEs are documented with details on onset/resolution time, severity, interventions, and outcomes.

### Drug accountability and medication compliance

#### Drug inventory management

During each follow-up visit, investigators will count the remaining medication or empty packaging returned by participants and inquire about adherence to the prescribed regimen (e.g., missed doses, dosage deviations). This information will be documented in the CRF to evaluate compliance.

#### Compliance assessment

Medication adherence is defined as strict adherence to the prescribed dosing schedule without unauthorized use of additional therapies. Compliance will be calculated using the medication counting method, supplemented by participant interviews when necessary:
$$\text{Compliance Rate }\left(\%\right)=\left(\text{Total medication consumed }/\text{ Total medication prescribed}\right)\times 100\%$$

### Data management

#### Data entry and modification

Prior to data entry, stringent controls are implemented to identify and correct errors, with all modifications documented and retained. Data managers collaborate with the principal investigator to establish data range checks and logic validation rules, encompassing automated system checks and manual medical reviews. Post-entry corrections require approval by the site principal investigator, ensuring traceability of all system operations through audit trails.

#### Database setup and data verification

This trial utilizes an electronic Case Report Form (eCRF) and Electronic Data Capture (EDC) system, designed to align with the protocol. Data managers implement automated logic checks and validation rules, supported by SAS software for comprehensive data verification. This includes identifying missing data, ensuring values fall within predefined ranges, and validating logical consistency. Investigators or clinical research coordinators (CRCs) input source data into the EDC, followed by multi-tiered verification (investigator, CRC, and monitor) and electronic signatures. Discrepancies are resolved through iterative queries, with all modifications documented in audit trails to ensure data integrity and traceability.

#### Blind review and locking

Unresolved queries are addressed during a blind review by sponsors, investigators, and statisticians to finalize the statistical analysis plan. The database is locked after joint authorization and undergoes initial unblinding for analysis. Post-trial, all data and documentation are archived for ≥2 years, with prior sponsor notification required before disposal.

#### Statistical analysis data set

Full Analysis Set (FAS): Includes all randomized participants who received at least one dose of the study drug and provided post-baseline effectiveness data. Missing primary outcomes are imputed using the last observation carried forward (LOCF) method under the intention-to-treat (ITT) principle. FAS serves as the primary population for effectiveness analyses.

Per-Protocol Set (PPS): A subset of FAS comprising participants with protocol adherence, complete baseline data, no major protocol deviations, and measurable primary endpoints. PPS is used for sensitivity analyses of primary outcomes.

Safety Set (SS): Encompasses all participants who received ≥1 dose and had safety assessments. Adverse event rates are calculated using SS.

#### Statistical analysis principles

No interim analysis will be conducted in this study. Following comprehensive data verification, missing values will be addressed, and erroneous entries or logical inconsistencies will be corrected to ensure data quality and completeness prior to formal statistical analyses. All analyses will be performed by investigators and independent biostatisticians using SAS 9.4 (SAS Institute Inc., Cary, NC) or equivalent software, with analysts blinded to treatment allocation. Hypothesis testing will employ two-tailed significance tests (except for pre-specified non-inferiority comparisons), with results reported as 95% confidence intervals (CI) and a significance threshold of α = 0.05. Statistical uncertainties and variability will be rigorously quantified to support robust clinical interpretations.

#### Missing values

For effectiveness endpoints, missing values are addressed using the LOCF method for the FAS. LOCF assumes that the last observed value remains unchanged for subsequent missing timepoints, providing a conservative estimate of treatment effects. This approach is widely used in clinical trials to minimize bias from participant dropout and ensure the robustness of ITT analyses.

For safety endpoints, no imputation is applied; analyses rely solely on observed data to avoid overestimating or underestimating adverse event rates. This ensures a more accurate representation of safety outcomes.

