#### Sample size calculation

Primary endpoints: throat pain resolution rate and overall effective rate

Parameters: Expected throat pain resolution rate: 91.43% (intervention group) vs. 76.92% (control group), non-inferiority margin (Δ) = 0.1 (Zhu et al., 2014), one-sided α = 0.025, power (1-β) = 80% (Chow et al., 2017). Initial calculation using PASS 15 software yielded 34 participants per group.

Adjustments:

A 20% dropout rate adjustment (n = 34/0.8 ≈ 43) required 44 participants per group (total 88).

To account for potential challenges in pediatric compliance and ensure robust statistical power, the final sample size was increased to 120 participants (60 per group). Since non-inferiority must be demonstrated for both primary endpoints to consider the trial successful, no adjustment for multiple testing is required in the analysis phase.

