#### Sensitivity and subgroup analyses

Analyses will be repeated in the per-protocol set to confirm robustness. Missing data will be handled via multiple imputations for sensitivity checks. Subgroup analyses will stratify by age (3–6 vs. 7–12 years) and baseline symptom severity (WBS score ≥7 vs. <7).

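### LOCF, the primary missing-data method, is called conservative; that does not hold for a non-inferiority test, where its bias can run either way

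*Protocol article*

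**What the plan says.** All references are to the protocol article.

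- *Statistical analysis data set*: "Missing primary outcomes are imputed using the last observation carried forward (LOCF) method under the intention-to-treat (ITT) principle". Also: "FAS serves as the primary population for effectiveness analyses". The FAS is defined thus: "Includes all randomized participants who received at least one dose of the study drug and provided post-baseline effectiveness data". The PPS needs a measurable primary endpoint and is described there as a set for sensitivity analyses.
- *Missing values* gives the reason for LOCF: "LOCF assumes that the last observed value remains unchanged for subsequent missing timepoints, providing a conservative estimate of treatment effects".
- *Sensitivity and subgroup analyses*: "Missing data will be handled via multiple imputations for sensitivity checks".
- *Analysis of primary outcome* tests non-inferiority by comparing the lower one-sided 97.5% bound of the risk difference (trial minus control) with −10 points. Both the FAS and the PPS must pass, on both primary endpoints.
- *Primary outcomes* defines resolution as a WBS score of 0 and effectiveness as a reduction of at least half, both at Day 5, from daily scores.

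**The concern.** A method that shrinks a difference is cautious when the aim is to show a difference. When the aim is to show that a deficit is smaller than 10 points, shrinkage helps the test drug. The justification in *Missing values* takes no account of which hypothesis is being tested.

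Throat pain is expected to fall day by day. A child who leaves on Day 1 or 2 still in pain is fixed as unresolved at Day 5, although many such children would have resolved. If both arms lose children in this way, a true deficit can be diluted. If the arms lose different numbers, the difference moves in favour of the arm that loses fewer. At stake is the chance that a drug truly 10 points worse passes, and whether readers can rely on the stated reassurance that the method errs on the safe side.

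**Working it through.** **The plan's own figure.** Inputs from *Sample size calculation*: "Expected throat pain resolution rate: 91.43% (intervention group) vs. 76.92% (control group), non-inferiority margin (Δ) = 0.1", one-sided α 0.025, power 80%. With unpooled variance,

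n = (1.960 + 0.842)² × [0.9143×0.0857 + 0.7692×0.2308] / (0.1451 + 0.10)² = 33.4, so 34 per group.

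This matches the plan. Dividing by 0.8 gives 43; the plan uses 44 and then 60.

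**Step 1: FAS alone, simple model.** From the plan: 60 per group, control rate 76.92%, margin 10 points, 20% dropout. Assumed: true XFOL rate 66.92% (exactly at the margin), the split of dropout by arm, and a share e = 30% of dropouts already at score 0 when last seen, the same in both arms.

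LOCF rate per arm = (1 − d) × p + d × e. Pass probability = Φ[(difference + 0.10)/SE − 1.96], with SE the unpooled standard error at n = 60.

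| Dropout XFOL / control | LOCF rates | Difference | SE | FAS error |
|---|---|---|---|---|
| none | 66.9% / 76.9% | −10.0 | 0.0815 | 2.5% |
| 20% / 20% | 59.5% / 67.5% | −8.0 | 0.0876 | 4.2% |
| 10% / 20% | 63.2% / 67.5% | −4.3 | 0.0868 | 9.6% |
| 20% / 10% | 59.5% / 72.2% | −12.7 | 0.0858 | 1.2% |

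For 10%/20%, varying e from 40% to 20% moves the error from 7.9% to 11.6%.

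**Step 2: let early resolution differ by arm.** A drug that is worse at Day 5 would normally trail earlier too. Exponential times to resolution matched to 66.92% and 76.92% give Day 2 rates of 35.8% and 44.4%. With 20% leaving each arm after Day 2:

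- XFOL: 0.8×0.6692 + 0.2×0.3576 = 60.7%
- Control: 0.8×0.7692 + 0.2×0.4437 = 70.4%
- Difference: −9.7 points

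Across last days 1 to 4 the difference runs from −9.1 to −10.1. In simulation (Wald bound, 2.7% with complete data), equal 20% dropout unrelated to outcome gives a FAS error of 2.6 to 3.1%. With a slower start to recovery (Weibull, shape 2) it is 2.8 to 3.9%. If only children still in pain at Day 2 leave, it is 4.2%. Under the exponential model, 10% XFOL/20% control dropout gives 5.5 to 7.6% and the reverse gives 0.9 to 1.3%.

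**Step 3: the actual decision rule.** Take the PPS as completers and require both sets to pass. The Step 1 scenarios then give joint errors of about 1.7% (20%/20%), 2.3 to 2.4% (10%/20%, e from 40% to 20%) and 0.9% (20%/10%). The Step 2 scenarios give at most 2.3%.

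**Step 4: a pattern that defeats both sets.** Suppose the children who leave are those who would have resolved by Day 5 but still score above 0 when last seen. LOCF codes them as failures and the PPS deletes them.

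- 10% XFOL / 20% control: FAS rates are 66.92 − 10 = 56.92% and 76.92 − 20 = 56.92%, difference 0. PPS rates are 0.5692/0.9 = 63.2% and 0.5692/0.8 = 71.2%, difference −7.9. Simulated error: FAS about 20%, PPS about 4.2%, joint about 4.1%.
- 5% / 15%: FAS difference 0, PPS difference −7.7, joint about 4.5%.
- Equal dropout of this kind: joint error below the complete-data 2.7%.

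All figures are for the resolution endpoint. The plan gives no expected overall effective rate, so the second endpoint cannot be sized; requiring it can only lower the joint error.

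**The case against.** A reader might infer two stronger things: that LOCF generally pulls the arms together, and that the trial's false non-inferiority rate is therefore 4 to 10%. The document supports neither.

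- **Direction.** The same arithmetic gives about 1% when XFOL loses more children. Under equal dropout unrelated to outcome, the difference barely moves once early resolution is allowed to differ by arm. The 4.2% for 20%/20% rests on giving both arms the same early resolution.
- **Decision rule.** The 4 to 10% figures are for the FAS alone. *Analysis of primary outcome* also requires the PPS and both endpoints, and in those scenarios the joint rate stays at or below about 2.4%.
- **Inputs.** The 20% is an allowance for sample size, not a forecast of missing Day 5 scores, and nothing in the document suggests that controls will leave more often.
- **The alternative.** Multiple imputation is already planned, and it is not automatically better. *Study discontinuation* lists progression needing rescue antibiotics. LOCF would usually leave such a child unresolved, whereas imputation under missing-at-random could credit some with recovery.
- **The FAS condition.** With daily scores, few dosed children should lack any post-baseline value.

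All of this stands, and it limits the size of the point. It does not rescue the justification. The PPS is no safeguard against outcome-related dropout that differs by arm (Step 4). Its status is also unclear, being a sensitivity set in one section and a condition of success in another.

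**Conclusion.** The statement that LOCF is conservative is wrong as a general claim for this non-inferiority test. LOCF can bias the FAS risk difference either way. The FAS-only error at the margin is about 4% with equal 20% dropout (2.6 to 3.9% if early resolution also differs by arm and dropout is unrelated to outcome), about 10% with 10% XFOL/20% control dropout, and about 1% with the reverse.

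The joint FAS and PPS rule holds the error at or below about 2.4% in those scenarios, but not in every one: it reaches about 4 to 4.5% on the resolution endpoint if recovering control children leave more often. Inflation of the trial's overall error is therefore possible but not established. Dropout timing, reasons and split by arm, the resolution curve, and the PPS taken as completers are all assumptions. This should be fixed, but it does not by itself invalidate the design.

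**What to change.** Before unblinding:

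1. Delete the sentence calling LOCF conservative.
2. Make the multiple imputation already planned, built on the daily WBS scores, the primary handling for both primary endpoints. Keep LOCF as a sensitivity analysis.
3. In the analysis, count children who discontinue for disease progression needing rescue antibiotics as non-responders; do not impute them under missing-at-random.
4. Add a tipping-point analysis that worsens the imputed XFOL outcomes until non-inferiority is lost.
5. Bring dosed children without a post-baseline score into the FAS through imputation, which also fits the intention-to-treat principle that the plan cites.
6. Reconcile the role of the PPS between *Statistical analysis data set* (sensitivity) and *Analysis of primary outcome* (condition for success).

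The cost is wording, a little programming and slightly wider intervals. No new data are needed.

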#### Demographic and baseline characteristics

Demographic and clinical baseline characteristics will be summarized by treatment and control group. Categorical variables (e.g., sex, ethnicity, medical history) will be reported as frequency counts (n) and percentages (%), with denominators reflecting available data. Continuous variables (e.g., age, height, weight, symptom duration) will be presented as means ± standard deviations (SD) for normally distributed data or medians with interquartile ranges (IQR) for non-normally distributed data. Missing data counts will be explicitly noted for all variables.

The following baseline parameters will be analyzed:1. Demographics: Age (years), sex (male/female %), height (cm), weight (kg), ethnicity.2. Medical History: Disease duration (days), allergies, pre-trial medications, prior episodes of pharyngitis/tonsillitis.3. Clinical Metrics: Baseline axillary temperature (°C), pharyngeal/tonsillar erythema severity (graded 0–3), laboratory values (WBC, CRP, ALT, AST, Scr).4. TCM Syndrome Scores: Baseline scores for sore throat, dry throat, cough, and pharyngeal signs using the TCM symptom grading scale.

No formal hypothesis testing will be performed for baseline comparisons; results will be interpreted descriptively to evaluate randomization balance.

### Analysis of primary outcome

Non-inferiority will be evaluated using a predefined margin (Δ = 10%), with the lower bound of the one-sided 97.5% CI for the risk difference (trial-control) between groups compared against −Δ. If this lower bound exceeds −Δ, non-inferiority will be established. The sample size was calculated based on this non-inferiority hypothesis with a one-sided significance level of 0.025, maintaining consistency between design and analysis phases. Between-group comparisons will utilize Chi-square tests for categorical outcomes, supplemented by mixed-effects logistic regression adjusted for baseline covariates (age, baseline WBS score). To ensure consistency in statistical inference, both FAS and PPS analyses must demonstrate non-inferiority to confirm the robustness of conclusions. The trial will be considered successful only when non-inferiority is established for both primary endpoints; therefore, no adjustment for multiple testing is necessary as this represents a conservative approach requiring success on all endpoints. Should non-inferiority be established, superiority testing will be conducted as a hierarchical testing procedure by assessing whether the lower bound of the 95% CI exceeds zero. Results will be reported as proportions, risk differences, and adjusted odds ratios with 95% CIs, with forest plots used to visually represent the treatment effects and their confidence intervals relative to both the non-inferiority margin and zero.

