#### Randomization, allocation concealment, and blinding

This multicenter trial will employ a central block randomization method (block size = 4) to ensure balanced allocation between the two groups, each comprising 60 participants. An independent statistician from the Center for Evidence-Based Chinese Medicine, Beijing University of Chinese Medicine, will generate the randomization sequence using SAS software, with site-specific coding ranges assigned to each participating center. Sequentially numbered, sealed, opaque envelopes will be used to maintain allocation concealment. Medications will be pre-packaged by personnel uninvolved in trial execution and stored in hospital pharmacies to preserve blinding.

Trained site investigators will enroll eligible participants and obtain informed consent. Upon enrollment, a designated third-party staff member will dispense study medications labeled with unique identifiers corresponding to the randomization list. To maintain blinding, both the participants and investigators will be unaware of treatment assignments throughout the trial. Blinding will also extend to outcome assessors and data analysts to minimize evaluation bias. All site personnel will undergo standardized training to ensure adherence to the trial protocol.

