#### Repeated measures and binary outcomes

Effective/resolution rates at Days 3 and 5 (WBS or TCM-assessed) and TCM symptom-specific scores will be analyzed using generalized estimating equations (GEE) with an exchangeable correlation structure to address repeated measurements. Binary outcomes (e.g., resolution yes/no) will be modeled via log-binomial regression, reporting risk ratios (RR) and 95% CI. Continuous TCM scores will use linear mixed-effects models, adjusted for baseline values and study center.

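### The non-inferiority comparison has no stated adjustment for centre, age or baseline pain, and the only adjusted primary model gives an odds ratio that cannot be read against the −10-point margin

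*Protocol article*

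**What the plan says.** All places are in the protocol article.

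- **Analysis of primary outcome, decision rule.** Non-inferiority is judged "with the lower bound of the one-sided 97.5% CI for the risk difference (trial-control) between groups compared against −Δ", with a margin of 10 points. It must hold for both primary endpoints, in FAS and in PPS. No adjustment of this risk difference is stated.
- **Same section, further analyses.** "Between-group comparisons will utilize Chi-square tests for categorical outcomes, supplemented by mixed-effects logistic regression adjusted for baseline covariates (age, baseline WBS score". The random effect is not named, and centre is not among the covariates.
- **Same section, reporting.** "Results will be reported as proportions, risk differences, and adjusted odds ratios with 95% CIs". The same sentence adds forest plots with the margin and zero as reference lines.
- **Randomization, allocation concealment, and blinding.** Central blocks of 4, "with site-specific coding ranges assigned to each participating center". Trial design gives three centres.
- **Repeated measures and binary outcomes.** For a secondary outcome: "Continuous TCM scores will use linear mixed-effects models, adjusted for baseline values and study center".

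**The concern.** If code ranges are made of whole blocks, allocation is balanced within each centre. An analysis that leaves centre out then uses a standard error that is too large whenever response differs between centres. Age and baseline WBS are also recorded before treatment, and the plan already treats them as prognostic by putting them in the supplementary model. Neither reaches the estimate that decides the trial.

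The adjusted model does use age and baseline WBS, but it answers on another scale. A reader who wants to know whether non-inferiority survives adjustment would be given an odds ratio with no margin attached. The chi-square test tests equality, so neither outcome of it bears on −10 points. At stake are some precision and a supporting analysis that cannot support.

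**Working it through.** **1. Inputs.** From Sample size calculation: expected resolution 91.43% (trial) and 76.92% (control), margin 0.10, one-sided α 0.025, power 80%, 34 per group before dropout, 60 per group finally. From Trial design: three centres, equal allocation. The documents give no centre-specific rates and no covariate effects, so those used below are assumptions.

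**2. The plan's own figure.** With unpooled variance,

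n = (1.960 + 0.842)² × (0.7692×0.2308 + 0.9143×0.0857) / (0.1451 + 0.10)² = 33.43, so 34 per group.

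This reproduces the stated figure. Design and decision rule share the risk-difference scale.

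**3. Can the odds ratio be read against the margin?** The odds ratio that equals a −10-point difference is [(p−0.10)/(1.10−p)] / [p/(1−p)] for control rate p. At p = 0.7692 this is (0.6692/0.3308)/(0.7692/0.2308) = 0.607.

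| Control rate | Odds ratio at −10 points |
|---|---|
| 60% | 0.667 |
| 70% | 0.643 |
| 76.92% | 0.607 |
| 85% | 0.529 |
| 90% | 0.444 |
| 95% | 0.298 |

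There is no fixed counterpart to the margin. Nor is zero a reference value for an odds ratio, whose null is 1.

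**4. What does leaving out centre cost?** Simulation with 200,000 runs, 20 per arm in each of three centres, comparing a simple unstratified interval with a size-weighted centre-stratified one. Each cell shows unstratified / stratified.

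| Assumed control rates | Type I error at −10 points | Power at true difference 0 | Mean SE at 0 |
|---|---|---|---|
| 76.92% in all | 0.027 / 0.029 | 0.269 / 0.274 | 0.0761 / 0.0748 |
| 70/77/84% | 0.026 / 0.029 | 0.265 / 0.276 | 0.0761 / 0.0740 |
| 62/77/92% | 0.023 / 0.029 | 0.259 / 0.294 | 0.0761 / 0.0715 |
| 50/85/95% | 0.016 / 0.030 | 0.239 / 0.327 | 0.0766 / 0.0668 |

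The first row is a control: with equal centres the stratified SE is still 1.7% smaller. This is a small-stratum artefact, √[(19/20)/(59/60)] = 0.983, so the simple stratified interval looks slightly too good throughout. The real gain is the between-centre share of the variance:

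- 70/77/84%: (2×0.07²/3)/(0.77×0.23) = 0.00327/0.1771 = 1.8%.
- 62/77/92%: (2×0.15²/3)/(0.77×0.23) = 0.015/0.1771 = 8.5%.
- 50/85/95%: 0.0372/0.1789 = 20.8%.

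Moderate spread therefore costs about 1 point of power and extreme spread about 9. At the planned difference of 0.1451 with moderate spread, power is 0.971 against 0.975, so the loss matters mainly if the two treatments are close. As centres diverge, the unstratified type I error falls (0.027 to 0.016): the test becomes conservative.

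**5. What does adding age, baseline WBS and centre gain?** In 1,500 simulated trials of 120 children in three centres, with an assumed log-odds slope of −0.35 per WBS point and centre effects of ±0.5, the variance was 0.00553 unadjusted and 0.00501 for the standardized risk difference. That is 1 − 0.00501/0.00553 = 9.4% smaller, or about 5% in SE. Other assumed effects gave gains from about −1% to 8%. At the low end, adjustment costs about 1% of variance.

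**The case against.** The strongest reply is that nothing here is broken. The decision rests on the risk difference, on the scale of both margin and sample size. The odds ratio is a supplement. The chi-square test appears in a separate sentence, and no conclusion is tied to either. An unadjusted risk difference is a valid estimator, and adjusting it for precision is optional. All of this stands.

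It can also be said that a mixed-effects model with one Day 5 outcome per child most naturally has centre as its random effect, and that naming it is detail for the analysis plan. That is a fair inference, though the text does not state it. It does not bring centre into the deciding risk difference, and it does not change the scale of the model's result. The randomization section never uses the word stratified; that reading follows from blocks combined with site-specific ranges and needs the ranges to be whole blocks. The plotting sentence can be read as meaning risk differences only, but it does not exclude odds ratios.

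A reader might infer three stronger things that the documents do not support:

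- **That omitting centre inflates false claims of non-inferiority.** The simulation shows the opposite direction.
- **That the chi-square test or the odds ratio decides non-inferiority.** The rule is the interval bound.
- **That the interval under-covers.** This would need a Wald interval, and the article names no method. If it were Wald, exact type I error at the planned 76.92% control rate would be 2.7%, close to the score method (2.66% and 2.59% at 48 and 60 per arm). It reaches 4.4% and 3.7% only at a 95% control rate, which the documents do not give.

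**Conclusion.** The point holds as an improvement in precision and coherence, not as a fault in validity. The deciding risk difference has no stated adjustment for centre, age or baseline WBS. The only adjusted primary analysis yields an odds ratio that has no fixed relation to −10 points, and so it cannot corroborate the conclusion.

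The precision at stake runs from none to about 8–9% of variance under the assumed covariate and centre effects. For centre alone it is about 1 point of power at moderate spread, and more only if centres differ greatly. These sizes depend on assumed inputs. The scale mismatch does not; it is arithmetic.

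**What to change.** In the analysis plan, before unblinding:

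1. Base the −10-point comparison on a risk difference standardized from a logistic model with arm, centre (fixed, three levels), age and baseline WBS, with its 95% interval, for both endpoints and in both FAS and PPS.
2. Support it with a centre-stratified Miettinen-Nurminen score interval, read against the same margin.
3. If the mixed-effects model is kept, name its random effect. Report odds ratios as descriptive and keep them off the plot that shows the margin and zero.
4. State that the chi-square test plays no part in the non-inferiority decision.

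One caution: at the planned rates there would be about 60×0.0857 + 60×0.2308 ≈ 19 children without resolution, for five coefficients (arm, two for centre, age, WBS). Say in advance that the stratified score interval decides if the model fails to converge or shows separation.

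Cost: plan wording and a little more programming, no new data, and a negligible loss of precision if the covariates turn out not to be prognostic.
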